## Abstract

**Background:**

Temporomandibular joint disorders (TMD) are common musculoskeletal conditions affecting the masticatory system, leading to pain and functional limitations. Despite various conventional treatments, parts of the 2021 Korean Medicine Standard Clinical Practice Guidelines for TMD remain unaddressed due to insufficient supporting evidence for certain modalities like intraoral balancing appliances. This study aims to investigate a novel approach, temporomandibular joint balancing therapy (TBT), as a potential effective treatment.

**Methods:**

This will be a single-center, randomized, assessor-blinded, parallel-group clinical trial. A total of 30 eligible participants aged 19 to 70 years with chronic TMD (VAS ≥ 40 mm for ≥ 3 months) will be randomized 1:1 to either the experimental group (TBT) or the control group (Transcutaneous Electrical Nerve Stimulation, TENS). Both interventions will be administered twice a week for 6 weeks (12 sessions). The primary outcome is the mean change in temporomandibular joint pain measured by the Visual Analog Scale (VAS, 100 mm) at 6 weeks compared to baseline. Secondary outcomes include worst TMD pain VAS, jaw range of motion (pain-free opening, maximum unassisted opening), Jaw Functional Limitation Scale (JFLS-8), DC/TMD Graded Chronic Pain Scale (GCPS 2.0), Treatment Expectancy Scale, Patient Global Impression of Change (PGIC), quality-adjusted life years (QALYs), EQ-5D, EQ-VAS, medical costs, lost productivity costs, and incremental cost-effectiveness ratio (ICER). Data will be collected at baseline, 6 weeks, and 10 weeks (for follow-up). Statistical analysis will compare outcomes between groups using appropriate methods, primarily intention-to-treat analysis.

**Discussion:**

This study protocol details a randomized controlled trial designed to provide robust evidence on the efficacy, safety, and economic feasibility of TBT for TMD. The findings are expected to contribute to the evidence base for TMD management, potentially informing future clinical practice guidelines, particularly concerning the use of intraoral balancing appliances in Korean medicine.

**Trial registration:**

This trial was retrospectively registered with the CRIS (http://cris.nih.go.kr). Registry: https://cris.nih.go.kr/cris/search/detailSearch.do?seq=29064, trial registration number: KCT0010382, date of registration: 3 April 2025.

**Supplementary Information:**

The online version contains supplementary material available at 10.1186/s12906-026-05303-8.

## Background

Temporomandibular joint disorder (TMD) encompasses a group of musculoskeletal and neuromuscular conditions affecting the temporomandibular joint (TMJ), masticatory muscles, and related structures [1]. TMD is commonly characterized by pain in the jaw, face, and head, as well as limited mandibular movement and joint sounds such as clicking and popping, all of which can significantly impair quality of life and daily functioning [2]. Its multifactorial etiology includes biomechanical stressors such as occlusal overloading and oral parafunctional habits including bruxism and clenching, hormonal influences like elevated estrogen levels, and psychological factors such as stress and anxiety. Understanding these contributing elements is necessary for accurate diagnosis and effective, individualized treatment planning [3].

The prevalence of TMD varies based on the target population, diagnostic criteria, and research methodology. Large-scale studies in the United States suggest that approximately 5% to 12% of the population experiences symptoms of TMD [4]. In Korea, recent nationwide cohort data from the National Health Insurance Service revealed that the age-standardized prevalence of clinically diagnosed TMD increased steadily from 604 per 100,000 persons in 2012 to 869 per 100,000 in 2020. The prevalence was particularly high among young adults, with the highest rates observed in individuals in their 20s (1,809 per 100,000), followed by teenagers and those in their 30s. Female patients consistently showed a 1.5-fold higher prevalence than males, aligning with global trends. Among the various TMD subtypes, internal derangement of the temporomandibular joint and unspecified joint pain were the most frequently recorded diagnoses [5].

Data from the Health Insurance Review & Assessment Service (HIRA) healthcare big data open system (accessed May 3, 2025) also reveals a consistent increase in patients diagnosed with TMD (Korean Standard Classification of Diseases K076) in South Korea from 2019 to 2023. Over the past five years, the number of patients with TMD treated at medical institutions—including hospitals, clinics, Korean medicine facilities, and dental centers—increased by approximately 25.78%, exceeding 560,000 individuals in 2023. Concurrently, the total medical expenditure associated with TMD increased significantly, rising from approximately 44.9 billion Korean Won (KRW) in 2019 to about 70.3 billion KRW in 2023, representing a 56.57% increase over the five years.

Conventional treatments remain the first-line approach for managing TMD, with interventions including physical therapy, manual therapy, exercise therapy, and reversible occlusal splints being most commonly applied [6]. Recent international clinical practice guidelines, such as those proposed by the International Network for Orofacial Pain and Related Disorder Methodology (INfORM) under the International Association for Dental, Oral, and Craniofacial Research (IADR) emphasize a patient-centered approach that prioritizes self-management strategies, education, and cognitive behavioral therapy (CBT), with surgical options reserved strictly for select, refractory cases [7]. Among non-invasive modalities, techniques such as joint mobilization, trigger point therapy, and posture-corrective exercises have demonstrated clinical utility [8]. Additionally, oral parafunctional habits, which can exacerbate pain and tension in muscles [9], are often addressed through behavioral modification and psychosocial support [10]. Meanwhile, pharmacological treatments, including NSAIDs, muscle relaxants, and antidepressants, are commonly used despite concerns about adverse effects and the lack of standardized regimens [11].

Emerging adjunctive therapies, such as transcutaneous electrical nerve stimulation (TENS) [12], low-level laser therapy (LLLT) [13], and therapeutic ultrasound [14], have garnered attention for their potential to alleviate pain and improve mandibular function, though long-term evidence remains limited. LLLT, in particular, has shown promising short-term results for muscle-related TMD pain [13], outperforming TENS and therapeutic ultrasound in meta-analyses [15]. Injection therapies, including botulinum toxin (BTX), corticosteroids, and hyaluronic acid, are selectively employed when conservative measures fail [16]. BTX injections into the masticatory muscles are increasingly utilized, offering temporary relief for myofascial pain and parafunctional activity [17], though concerns about functional impairment and the need for repeated administration persist [18]. Despite the wide range of available therapies, clinical outcomes often vary based on individual patient characteristics. Therefore, multidisciplinary, personalized treatment planning and further high-quality studies are needed to guide evidence-based decision-making. In addition, it is noteworthy that despite the short-term symptom relief achieved by most conservative treatments, their long-term efficacy remains uncertain in many cases [19].

This study aims to evaluate the efficacy, safety, and cost-effectiveness of TMJ balancing therapy (TBT) for TMD in comparison to TENS, a widely used conservative treatment modality. TBT is a structural medicine approach designed to correct misalignments of the entire spine and body primarily by restoring the balance of the TMJ and the axis (C2 cervical vertebra). Unlike conventional treatments that often focus on symptom management or localized interventions, TBT offers a distinctive value proposition by addressing the underlying structural and neurological imbalances contributing to TMD. TBT regards the TMJ as a central joint that influences the structural and functional balance of the brain, cervical muscles, nervous system, and the spinal column. By restoring the optimal multidimensional balance position of the TMJ using an intraoral balancing appliance, TBT aims to address both structural and neurological imbalances that are closely linked to the misalignment of the TMJ. Once the TMJ is realigned, patients perform stretching and postural exercises to reinforce proper alignment, particularly the C2 vertebra, thereby promoting spinal stability and nervous system regulation [20].

The rationale for this approach is supported by radiographic studies demonstrating a close anatomical and functional link between the TMJ and the upper cervical spine (particularly C2). For example, Nagashima et al. reported a correlation between the occiput-C2 (O-C2) angle and the mandibular gonion-C2 distance, indicating that a decreased O-C2 angle can lead to posterior mandibular displacement and pharyngeal narrowing [21]. Similarly, Thomas et al. found that a significant majority (83%) of their study subjects exhibited posteriorly pitched crania, with 75% showing posteriorly compressed TMJs and 80% displaying rightward rotation of the atlanto-occipital joint [22]. These findings collectively suggest the dynamic structural relationship between the TMJ and C2, emphasizing the need for a comprehensive approach to TMJ disorder that considers the connections between the TMJ, cervical spine, skull, and overall body balance, especially when structural issues have become chronic [20].

In light of this evidence, therapies such as TBT that address the dynamic interrelationship between the jaw, cervical spine, and postural alignment may offer clinical benefits for patients with chronic or recurrent TMD. Formerly referred to as Functional Cerebrospinal Therapy (FCST), TBT has been reported to yield long-term symptom improvement in challenging conditions such as chronic recurrent TMJ dislocation and other treatment-resistant disorders [23]. Given that TMD is often associated with structural imbalances resulting from maladaptive oral and postural habits, conventional treatment modalities may fail to fully correct these underlying biomechanical dysfunctions. Therefore, when TBT is applied to correct these structural issues, its therapeutic effects are expected to be more sustainable, particularly in long-term follow-up.

## Methods/design

### Study design

This study will be a single-center, randomized, assessor-blinded, active-controlled, parallel-group clinical trial designed to evaluate the efficacy, safety, and cost-effectiveness of TBT for TMD. A total of 30 participants will be recruited and randomly assigned in a 1:1 ratio to the TBT experimental group and TENS control group. The study consists of a screening visit, 12 treatment visits over 6 weeks (twice weekly), and a follow-up visit at week 10. The detailed study design is summarized in Fig. 1; Table 1. This protocol adheres to the Standard Protocol Items: Recommendations for Interventional Trials (SPIRIT) 2013 guidelines and checklist (Supplementary material 1) [24]. The flowchart of this study is shown in Fig. 1. The SPIRIT schedule of enrollment, interventions, and assessments is shown in Fig. 2.

**Fig. 1 Fig1:**
[figure not shown]
Flowchart of the study plan. TBT; temporomandibular joint-balancing-therapy, TENS; transcutaneous electrical nerve stimulation

**Table 1 Tab1:** Eligibility criteria

**Inclusion Criteria**:
1. Men and women aged 19–70 years
2. Patients who experience intermittent pain persisting for more than three months in either or both temporomandibular joints (TMJ) according to the Diagnostic Criteria for Temporomandibular Disorders (DC/TMD)
3. Patients whose average pain intensity in the most painful TMJ (for bilateral pain, the more painful side was considered) over the past week is ≥ 40 mm on the Visual Analogue Scale (VAS)
4. Patients who present with localized pain in the TMJ or surrounding areas (temple, ear canal, or preauricular area) induced by jaw movement, function, or parafunction
5. Patients whose pain is confirmed by palpation of the temporalis muscle, masseter muscle, or the lateral pole of the mandibular condyle, corresponding to myalgia, myofascial pain, or arthralgia, or those with a headache located in the temporal region that is provoked or aggravated by jaw movement and is reproducible upon examination
**Exclusion Criteria**:
1. Patients with a history of surgery related to the TMJ
2. Patients with multiple pain disorders (e.g., rheumatoid arthritis) or neurological disorders (e.g., brain tumor, stroke, trigeminal neuralgia) that could interfere with treatment effects or the interpretation of results
3. Patients who are currently taking steroids, immunosuppressants, psychiatric medications, or other drugs that could affect study outcomes
4. Patients who have started or discontinued medications that could influence pain, such as non-steroidal anti-inflammatory drugs (NSAIDs), within the past month
5. Patients deemed by the investigator to be unsuitable for participation in the study (e.g., those with implanted electrical devices such as pacemakers)

**Fig. 2 Fig2:**
[figure not shown]
Schedule of enrollment, interventions, and outcome measurements

### Participants

Participants will be recruited through advertisements in local hospitals and community centers. Eligibility will be assessed via a structured interview and physical examinations by a trained doctor of Korean Medicine at Daejeon Korean Medicine Hospital of Daejeon University, according to the eligibility criteria shown in Table 1. All participants must manually sign a written informed consent form (ICF) before any study procedures.

### Sample size calculation and statistical hypotheses

The sample size for this trial was determined based on statistical calculations and reference to a previous randomized controlled trial with a similar design [25]. A total of 30 participants (15 in the intervention group and 15 in the control group) will be recruited, considering a 20% dropout rate. This allows for 24 evaluable subjects (12 per group) for the primary analysis.

The hypothesis of this study is as follows:$$\mathrm{H}_o\left(\text{null hypothesis}\right):\mu\mathrm{t}=\mu\mathrm{c}$$$$\mathrm{H}_1\left(\text{alternative hypothesis}\right):\mu\mathrm{t}\neq\mu\mathrm{c}$$

µt denotes the mean change in Visual Analog Scale (VAS, mm) score from baseline to 6 weeks in the experimental group (TBT), and µc is the mean change in VAS (mm) score from baseline to 6 weeks in the control group (TENS). The experimental and control groups will be recruited in a one-to-one ratio.

The calculation assumed a two-sided significance level (α) of 0.05, a type II error (β) of 0.1 (power = 90%), and a 1:1 allocation ratio. A previous RCT with a similar design (10-week intervention, 12 sessions) reported a mean difference of − 2.53 in VAS between groups, with a pooled standard deviation (SD) of 0.96 (Rezaie et al., 2022). For conservative estimation, this study applied a smaller mean difference (–2) and larger SD (1.5).

The required sample size per group was calculated using the formula for a two-sample t-test:

Calculation formula: $$\:\frac{2{({z}_{1-\frac{\alpha\:}{2}}+{z}_{\beta\:})}^{2}\times\:{\sigma\:}^{2}}{\left|{\mu\:}_{T}-{\mu\:}_{c}\right|}=\:\frac{2{(1.96+1.28)}^{2}\times\:{1.5}^{2}}{{(-2)}^{2}}=11.81\approx\:12$$  

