### Outcome measures

#### Primary outcome: visual analog scale

The primary outcome measure is the average temporomandibular joint pain Visual Analog Scale (VAS, 100 mm) score over the past week. It will be assessed at Week 0 (Baseline) and Week 6 (Primary endpoint).

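### The stated 90% power comes from a normal approximation labelled as a t-test (exact t-test: 87.7% at 12 per group), and the planning difference and SD carry no unit although the endpoint is in mm

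*Protocol article*

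**What the plan says.** Everything at issue except the endpoint definition and the analysis model is in the section on sample size calculation and statistical hypotheses.

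- **Parameter.** The experimental-group mean µt "denotes the mean change in Visual Analog Scale (VAS, mm) score from baseline to 6 weeks in the experimental group (TBT"; µc is defined in the same way for TENS.
- **Error rates.** "The calculation assumed a two-sided significance level (α) of 0.05", together with "a type II error (β) of 0.1 (power = 90%), and a 1:1 allocation ratio".
- **Planning values.** The section cites a previous trial with a mean difference of -2.53 and a pooled SD of 0.96. It then says that, to be conservative, "this study applied a smaller mean difference (–2) and larger SD (1.5". No unit stands beside any of these four numbers.
- **Method.** "The required sample size per group was calculated using the formula for a two-sample t-test". The formula that follows uses the normal quantiles 1.96 and 1.28 and gives 11.81, rounded to 12 per group. Allowing 20% dropout, 15 per group are recruited.
- **Endpoint.** Under the primary outcome heading: "The primary outcome measure is the average temporomandibular joint pain Visual Analog Scale (VAS, 100 mm) score over the past week". Inclusion criterion 3 in Table 1 requires at least 40 mm on this scale.
- **Primary analysis.** The primary outcome analysis section plans a baseline-adjusted ANCOVA on all randomised participants, with multiple imputation for missing values.

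**The concern.** Two statements in the sample size section do not match what surrounds them.

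First, the text names a t-test, but the calculation uses normal quantiles and so treats the SD as known. At 12 per group the difference between the two is visible, so the stated power is not the power of the named test.

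Second, the parameter is defined in mm, but the numbers put in for it make sense only on a 0-10 scale. The only unit in that section is mm, so nothing stops a reader from taking the target difference as 2 mm.

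The target difference and the power are what readers turn to when they judge a non-significant result. A trial planned around 20 mm says little about much smaller differences, and a reader who takes the target as 2 mm would think otherwise.

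**Working it through.** **Inputs (sample size section):** α = 0.05 two-sided; power 90%; 1:1 allocation; difference 2; SD 1.5; 12 evaluable per group; 20% dropout.

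**1. Reproduce the plan's figure.**
n per group = 2 × (1.96 + 1.28)² × 1.5² / 2² = 2 × 10.4976 × 2.25 / 4 = 11.81, so 12. Dropout: 12 / 0.8 = 15 per group, 30 in total. The plan's numbers reproduce. Under the same normal approximation, power at 12 per group is 90.4%.

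**2. Exact two-sample t-test with the same inputs.**
Standardised difference d = 2 / 1.5 = 1.33. Noncentrality = d × √(n/2); degrees of freedom = 2n − 2.

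| n per group | df | noncentrality | two-sided 5% critical t | power |
|---|---|---|---|---|
| 12 | 22 | 3.27 | 2.074 | 87.7% |
| 13 | 24 | 3.40 | 2.064 | 90.3% |
| 15 (no dropout) | 28 | 3.65 | 2.048 | 94.1% |

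At the plan's evaluable number the shortfall is 90 − 87.7 = 2.3 percentage points, or one evaluable participant per group.

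**3. Units.**
On a 0-10 scale, -2 and 1.5 correspond to 20 mm and 15 mm. The ratio is 20 / 15 = 2 / 1.5 = 1.33, so n and power are the same in either unit. What changes is the target difference a reader takes away: 20 mm or 2 mm. An SD of 1.5 mm is not credible on a 100-mm scale with entry at 40 mm or more, so the 0-10 reading is the plausible one. The article does not say so.

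Assuming an SD of 15 mm, the half-width of a 95% confidence interval at 12 per group is 2.074 × 15 × √(2/12) = 12.7 mm.

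**4. Planned ANCOVA.**
The power depends on two things the article does not give: the correlation r between baseline and Week 6, and whether 1.5 is the SD of the score or of the change. At 12 per group (df 21):

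- *1.5 is the SD of the score.* Residual SD = 1.5 × √(1 − r²). Allowing for chance baseline imbalance, power is 87% at r = 0.2, 89% at 0.3, 91% at 0.4 and 94% at 0.5. It reaches 90% at r of about 0.35.
- *1.5 is the SD of the change*, with equal variances at both times assumed. Residual SD = 1.5 × √((1 + r)/2). Without the imbalance allowance, power is 99.3% at r = 0, 97.1% at 0.3 and 94.9% at 0.5. It stays at 90% or more up to r of about 0.75 to 0.8; the lower value includes the allowance.

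The two readings move in opposite directions as r rises.

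**5. Printed formula.**
The symbolic denominator is the absolute difference without a square. The next expression in the same equation has (-2)² and gives 11.81.

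**The case against.** The strongest reply is that nothing in the design changes. The normal approximation is a routine planning tool, and 12 per group and 30 in total follow from it exactly. The gap to the exact t-test is one participant per group, and it arises only if the full 20% drop out. The planned analysis is an ANCOVA on all randomised participants, not an unadjusted t-test. The unit is a label and leaves n untouched. All of this stands, and it limits the point to a restatement. It does not remove the mismatch between the named test and the printed formula, or supply the missing unit.

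Several stronger readings are tempting, and the documents do not support them:

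- **That the sample size is wrong, or should be 24 per group.** The figure of 23.6 comes from using the unsquared denominator. The numeric step squares it, so this is a typographical slip.
- **That the trial claims 90% power for 2 mm.** No unit is printed beside the planning values, so a reader could infer this, but the article never states it. Computing power for a literal 2 mm against a converted SD of 15 mm combines two readings that the article never pairs.
- **That 87.7% is the power of the primary analysis.** It is the power of the test named in the sample size section. The ANCOVA's power may be slightly lower or clearly higher.
- **That ANCOVA reaches 90% only above some modest correlation.** This holds only if 1.5 is the SD of the score. The parameter is defined as a change, and if 1.5 is the SD of the change, a low correlation helps.

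**Conclusion.** The point holds as a matter of reporting. The stated 90% is a normal-approximation figure attributed to a t-test. For the named test at the stated evaluable number, power is 87.7%, which is 2.3 points lower. The target difference and SD lack a unit in a section that defines the parameter in mm, which leaves a possible tenfold misreading of the target.

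The sample size stands: it reproduces from the plan's inputs, and the unit does not affect it. The 87.7% rests on the plan's own difference and SD, an unadjusted two-sided test and 12 evaluable per group. The conversion to 20 mm and 15 mm is an inference from the endpoint scale and the entry threshold, and has to be confirmed against the source trial.

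**What to change.** Keep n = 30 and correct the text of the sample size section:

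1. State the target difference and SD in mm (20 mm and 15 mm, once the scale of the source trial is confirmed), and give the unit for the cited -2.53 and 0.96 as well.
2. Describe the formula as a normal approximation and give power as about 88% for the two-sample t-test at 12 per group. Alternatively, give power for the planned ANCOVA, with the assumed correlation between baseline and Week 6 and a statement of whether 1.5 is the SD of the score or of the change.
3. Square the difference in the symbolic denominator (minor, typographical).

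The cost is a few lines of text. Recruitment, randomisation and the analysis are unaffected. If the t-test figure is used, the stated power becomes slightly less favourable.

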### Interventions

Participants in both groups will receive a total of 12 treatment sessions, administered twice a week for 6 consecutive weeks.

